# Impact of deprescribing intervention on potentially inappropriate medications and clinical outcomes among hospitalized older adults in Malaysia: a randomized controlled trial (REVMED RCT) protocol

**DOI:** 10.1186/s40545-023-00621-5

**Published:** 2023-10-03

**Keywords:** Polypharmacy, Deprescribing, Potentially inappropriate medications, Geriatrics, Fall, Readmission, Quality of life

## Abstract

**Background:**

Polypharmacy and the use of potentially inappropriate medications (PIMs) are prevalent among older patients admitted to hospitals, posing a heightened risk of adverse drug events. This trial aims to evaluate the effectiveness of a pharmacist-led deprescribing intervention in reducing medications, PIM and improving clinical outcomes, using the locally developed Malaysian Potentially Inappropriate Prescribing Screening tool in Older Adults (MALPIP).

**Methods:**

This is an 18-month cluster-randomized, open-label, parallel-arm controlled trial conducted at 14 public hospitals in the Perak state of Malaysia. Patients aged 60 and above, who have at least one medication and one comorbidity are eligible. A stratified-cluster randomization design is employed, with 7 hospitals assigned to the control arm and 7 hospitals assigned to the intervention arm. The MALPIP screening tool will be used in the intervention group to review the medications. If PIM is detected, the pharmacists will discuss with doctors and decide whether to stop or reduce the dose. The primary outcomes of this trial are the total number of medications and number of PIM. The secondary outcomes include fall, emergency department visits, readmissions, quality of life and mortality. Outcomes will be measured during enrolment, discharge, 6, 12, and 18 months.

**Discussion:**

This REVMED trial aims to test the hypothesis that a pharmacist-led deprescribing intervention initiated in the hospital will reduce the total number of medications and PIM 18 months after hospital discharge, reducing fall, emergency department visits, readmissions, mortality and lead to improvement in quality of life. Trial findings will quantify the clinical outcomes associated with reducing medications and PIM for hospitalized older adults with polypharmacy.

*Trial registration number:* This trial was prospectively registered at clinicaltrials.gov (NCT05875623) on the 25th of May 2023. NCT05875623 Clinicaltrials.gov URL: NCT05875623 registered on 25th July 2023.

## Introduction

Globally, the world is ageing. The United Nations estimates that by 2050, one in six people in the world will be over age 65 (16%), up from one in 11 in 2019 (9%) [1]. While this can be considered one of the successes of the twenty-first century, older individuals are more likely to experience multiple health issues, thus requiring more medication than their younger counterparts. This poses another problem for many health systems, as the prescription of various medications can lead to drug-related problems, including polypharmacy, the use of potentially inappropriate medications, and challenges with medication adherence [2, 3]

Polypharmacy, which is commonly defined as regular use of five or more prescription drugs [4] increases the likelihood of an adverse drug event (ADE) and hospitalization [5, 6]. In addition, polypharmacy is also associated with an increased risk of multiple falls [7, 8] and the use of potentially inappropriate medications (PIM) among older adults [9].

Deprescribing has been suggested to reduce the number of medications and mitigate the potential for adverse drug events resulting from inappropriate medication use in older adults [10]. To guide deprescribing, several explicit tools have been developed to identify potentially inappropriate prescribing in older adults. The most widely used explicit PIM tool is the American Geriatrics Society Beers' criteria for Potentially Inappropriate Medication Use in Older Adults. Another commonly used tool is the Screening Tool of Older Person's Prescriptions (STOPP) and the Screening Tool to Alert doctors to Right Treatment (START) to facilitate the detection of potential omission and commission errors in prescribing [11, 12].

Evidence from randomized controlled trials has demonstrated the effectiveness of using explicit PIM criteria in reducing PIM. Systematic review of randomized controlled trials demonstrated that deprescribing reduced medication burden and positively impacts health-related quality of life, costs, and hospitalization [13]. Deprescribing interventions also reduced medication errors and potential drug–drug interactions [14–16]. While studies have demonstrated the effectiveness of explicit PIM criteria in improving older patients’ outcomes, most relied on the Western PIM criteria, such as START-STOPP and Beers criteria [17–19].

In the context of deprescribing interventions, it is crucial to consider the diverse population demographic, pharmacogenomics, prescribing practices, and cultural factors that exist within different regions [20–22]. By taking these factors into consideration, the intervention is better aligned with the specific needs and characteristics of the target population. The adoption of a tailored approach in this trial acknowledges the distinct differences that may arise within the Asian population, particularly in a country like Malaysia.

## Methods

### Aim of the trial

This trial aims to assess the effectiveness of a pharmacist-led deprescribing intervention using the locally developed Malaysian Potentially Inappropriate Prescribing Screening tool in Older Adults (MALPIP) in reducing chronic medications, PIMs and improving clinical outcomes among older adults who have recently been hospitalized.

### Outcome measures

The primary outcome of the trial is the total number of chronic medications and PIM taken by older adults at five time-points (admission, discharge, 6 months, 12 months and 18 months post-randomization).

The secondary outcomes include fall events, number of emergency department visits, number of ADE-related and all-cause readmissions to the hospital, and mortality at 6 months, 12 months, and 18 months post-randomization. The total number of pharmacists' interventions and acceptance by doctors will be measured at discharge. The quality of life will be measured at admission, discharge, 6 months, 12 months, and 18 months post-randomization (Table 1).

**Table 1 Tab1:** Primary and secondary outcomes, instruments, and time-points

	Instruments	Time-points
Primary outcome		
1. PIM	MALPIP	Admission, discharge, 6 months, 12 months and 18 months
2. Chronic medications	Medication prescribed continuously for more than 28 days prior to the assessment day	Admission, discharge, 6 months, 12 months and 18 months
Secondary outcome		
1. Recommendations made by pharmacists and accepted by physicians	Pharmacists’ pharmacotherapy review form and patients’ case note	Discharge
2. Fall event	Medical records and self-reported using ICD-10 codes	discharge, 6 months, 12 months and 18 months
3. Emergency Department (ED) visit	Medical records and self-reported	6 months, 12 months and 18 months
4. ADE-related and all-cause readmissions	Medical records and self-reported	6 months, 12 months and 18 months
5. Quality of life	EQ-5D-5L	Admission, discharge, 6 months, 12 months and 18 months
6. Survival status	National Registration Department database	discharge, 6 months, 12 months and 18 months

### Overview of trial design

This is an 18-month cluster-randomized, open-label, multicenter, parallel-arm controlled trial at 14 public hospitals in the Perak state of Malaysia among older patients (≥ 60 years old). The deprescribing interventions will be led by ward pharmacists who had at least 5 years of clinical pharmacy experience.

The ward pharmacists undertake a comprehensive review of the patient's medication before performing the deprescribing interventions.

### Trial setting

The trial will be conducted in the state of Perak, which has one of the highest proportion (8.9%) of older adults aged 65 years and above in Malaysia [23]. The state is served by 14 public hospitals spread across the 10 administrative districts. In this study, seven hospitals will be randomized to intervention with the remaining seven hospitals serving as the control group (Fig. 1). In order to ensure a representative population is recruited, both general medicine wards or geriatric wards will be selected from each hospital, from both female and male wards.

**Fig. 1 Fig1:**
[figure not shown]
Distribution of 14 public hospitals across 10 districts in Perak State: treatment allocation, annual admission, and sample size

### Randomization

A stratified-cluster randomization design will be adopted for this trial, with the 14 hospitals serving as the unit of randomization. This design was chosen specifically to address the potential "contamination" effect that may arise among individuals within the same ward. The cluster design effectively controls for the potential "contamination" effect that may arise among individuals (pharmacists, doctors, patients) within the same ward, where changes in one individual's behaviour may have the potential to influence others. Furthermore, this approach offers the advantage of significant time savings compared to individual randomization. The principal investigator performed the randomization.

Given that larger and smaller hospitals may have different administrative capacities, it was crucial to ensure a balanced distribution of patients across both intervention and control arms. To achieve this, trial sites were stratified and clustered based on the number of yearly admissions in each hospital as follows:i.Hospitals with 4001–5000 yearly admissions (total of 5 hospitals; intervention: 3; control: 2)ii.Hospitals with 3001–4000 yearly admissions (total of 6 hospitals; intervention: 3; control: 3)iii.Hospitals with 1500–3000 yearly admissions (total of 3 hospitals; intervention: 1; control: 2).

This approach ensures a balanced and comparable distribution of patients in both the intervention and control groups.

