### Sample size calculation

Sample size was calculated based on the primary outcome: the reduction in the mean number of PIM in discharge. According to Wehling et al. [24], the mean number of PIMs at discharge for the intervention group was 0.15, while the mean number of PIMs at discharge for the control group was 0.28 [24]. For an alpha risk of 0.05 and a 90% power, standard deviation 0.39, it was estimated that 189 patients would be needed per arm (378 patients in total) to detect a 0.13 reduction in the mean number of PIM [24]. Projecting a subject dropout rate of 25%, the total number of subjects required will be 500, or 250 per arm. The number of samples per trial site will be stratified based on yearly admissions. Sample size was calculated using Power and Sample size online calculator, compare two proportions, two-sample, two-sided equality test [25].

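### The 3:2, 3:3 and 1:2 split of the size strata is the closest available, but it does not ensure a balanced hospital-size mix as the protocol states

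*Protocol article*

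**What the plan says.** The Randomization section of the protocol article describes a stratified-cluster design "with the 14 hospitals serving as the unit of randomization". It gives the reason for stratifying: larger and smaller hospitals may have different administrative capacities, so "it was crucial to ensure a balanced distribution of patients across both intervention and control arms". Three strata are listed:

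- "Hospitals with 4001–5000 yearly admissions (total of 5 hospitals; intervention: 3; control: 2"
- "Hospitals with 3001–4000 yearly admissions (total of 6 hospitals; intervention: 3; control: 3"
- "Hospitals with 1500–3000 yearly admissions (total of 3 hospitals; intervention: 1; control: 2"

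The section closes with "This approach ensures a balanced and comparable distribution of patients in both the intervention and control groups".

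Trial setting gives the overall ratio: "seven hospitals will be randomized to intervention with the remaining seven hospitals serving as the control group". Sample size calculation sets 500 patients, 250 per arm, and adds: "The number of samples per trial site will be stratified based on yearly admissions". According to its caption, Figure 1 shows allocation, annual admissions and sample size by hospital, but the figure is not available in the text reviewed.

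**The concern.** Two of the three strata hold an odd number of hospitals, so neither can be halved. The two remainders tilt the same way: the intervention arm has the extra large hospital and the control arm has the extra small one. Site targets then depend on yearly admissions, which can carry the difference from hospitals to patients. On hospital size, the characteristic that defines the strata, the design does not have the property that the closing sentence claims for it.

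What is at stake is comparability. If hospital size is related to the number of potentially inappropriate medications (PIM), chronic medications or readmissions, part of an unadjusted difference between arms could reflect where patients were recruited. With only 14 clusters, one hospital more or fewer in a stratum is a visible share of an arm. The methods named under Data analysis (repeated measures ANOVA and independent t-tests) do not mention the size stratum, although a separate analysis plan may.

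**Working it through.** **Inputs from the protocol.** Hospitals by stratum (large, medium, small): 5, 6, 3. Intervention: 3, 3, 1. Control: 2, 3, 2. Stratum limits in yearly admissions: 4001–5000, 3001–4000, 1500–3000. Planned patients: 250 per arm.

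**Assumptions, because Figure 1 is not shown.** Site targets are proportional to admissions within each arm. Each stratum's mean is taken at its midpoint (4500.5, 3500.5, 2250), then varied over the stated limits.

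**1. Is this the best available split?** For a 7:7 allocation with l, m and s intervention hospitals in the three strata, measure imbalance as |2l − 5| + |2m − 6| + |2s − 3|. The first and last terms are each at least 1, so the minimum is 2. Over all 7:7 splits, only 3/3/1 and its mirror image 2/3/2 reach 2. The next best (2/4/1 and 3/2/2) score 4.

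**2. Patient mix at the midpoints.** Share of stratum k = hospitals in k × mean admissions in k ÷ arm total.

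- Intervention total: 3 × 4500.5 + 3 × 3500.5 + 1 × 2250 = 26,253
- Control total: 2 × 4500.5 + 3 × 3500.5 + 2 × 2250 = 24,002.5

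| Stratum | Intervention | Control |
|---|---|---|
| Large | 13,501.5 / 26,253 = 51% (about 129 of 250) | 9,001 / 24,002.5 = 38% (about 94) |
| Medium | 10,501.5 / 26,253 = 40% (about 100) | 10,501.5 / 24,002.5 = 44% (about 109) |
| Small | 2,250 / 26,253 = 9% (about 21) | 4,500 / 24,002.5 = 19% (about 47) |

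**3. Sensitivity, stratum means equal in the two arms.** Varying the three means over their limits, the large-hospital share is 12 to 16 points higher in intervention, and the small-hospital share is 7 to 14 points higher in control.

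**4. Sensitivity, stratum means free to differ between arms.** The large-hospital gap runs from −1 to +28 points. The low end needs opposite extremes in the two arms: intervention at 4001, 4000 and 3000 gives 12,003 / 27,003 = 44.5%; control at 5000, 3001 and 1500 gives 10,000 / 22,003 = 45.4%.

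**5. Equal stratum quotas in each arm.** Summed midpoint admissions are 5 × 4500.5 = 22,502.5, 6 × 3500.5 = 21,003 and 3 × 2250 = 6,750, in total 50,255.5. Multiplying each share by 250 gives about 112, 104 and 34 patients per arm. Per hospital this is about 37, 35 and 34 in intervention and 56, 35 and 17 in control, against 43, 33, 21 and 47, 36, 23 under proportional targets.

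**6. Precision cost of those quotas.** With intracluster correlation ρ and cluster sizes m, the variance of the difference in patient-weighted arm means is proportional to (1 − ρ) × 500 + ρ × Σm². Σm² is about 18,784 under proportional targets and 19,398 under equal quotas. At ρ = 0.01 the ratio is 689.0 / 682.8 = 1.009; at ρ = 0.10 it is 2,389.8 / 2,328.4 = 1.026. The values of ρ are assumed; the protocol gives none.

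**The case against.** The strongest reply is that the protocol could not have done better with these strata. Arms are equal in hospitals (7:7) and in planned patients (250:250), the medium stratum is exactly halved, and step 1 shows that no other 7:7 split comes closer. Balance is never defined as an identical size mix. All of that stands: this is a limit of strata with odd counts and not an allocation error. It does not rescue the word *ensures*, because a headcount of 250 per arm needs no size strata. Those strata are there for the hospital-size mix, and that is what differs.

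The second reply is that the site targets are in Figure 1 and may already offset the difference. This also stands, and it makes the patient percentages conditional.

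A reader might infer more than the document supports:

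- *That the arms will miss 250 each.* This would need targets proportional to admissions across all sites pooled. The protocol does not state such a rule and does fix 250 per arm.
- *That every rule proportional to admissions within arm must leave an imbalance.* Step 4 shows that the gap can vanish at the extremes of the stratum limits.
- *That the comparison is biased by a known amount.* The protocol says only that administrative capacity may differ with size. It gives no relation between size and any outcome, and a one-hospital remainder does not by itself bias a randomised comparison.

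Finally, an article may leave adjustment for stratum to the analysis plan, so its absence here is not an error in itself. It is the natural remedy all the same.

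**Conclusion.** The statement that the approach ensures balance is too strong. The size mix is 3/3/1 against 2/3/2 by construction, although that is the best 7:7 split available. With targets proportional to admissions within arm and similar stratum means, the large-hospital share of patients is about 12 to 16 percentage points higher in intervention (51% v 38% at assumed midpoints), and the small-hospital share is 7 to 14 points higher in control (19% v 9%). These figures rest on both assumptions and must be checked against Figure 1. The consequence for PIM, medication counts or clinical outcomes cannot be quantified from the document. The point is moderate: the claim needs correcting and the repair is cheap, but neither the allocation nor the sample size is shown to be wrong.

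**What to change.** 1. In Randomization, replace the claim that balance is ensured with the facts: 3 large, 3 medium and 1 small hospital in intervention, 2, 3 and 2 in control, which is approximate balance and the closest 7:7 split for these strata. This costs only wording.
2. Include the size stratum used for randomisation as a factor in the primary and secondary analyses. This needs no further data and spends two degrees of freedom for three strata, which should be weighed against having 14 clusters. The small stratum in the intervention arm still rests on a single hospital, so there size and hospital cannot be separated.
3. If the Figure 1 targets do not already do so, and can still be changed, set the same quota per size stratum in both arms: about 112, 104 and 34 at the assumed midpoints, to be recalculated from actual admissions. The total stays at 500. The cost is more uneven cluster sizes in the control arm (about 56, 35 and 17 per hospital), a higher recruitment load for the one small intervention hospital (about 34 rather than 21), and about 1% to 3% more variance at an assumed intracluster correlation of 0.01 to 0.10.

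If site targets are already fixed, items 1 and 2 are sufficient.

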### Sample size calculation

Sample size was calculated based on the primary outcome: the reduction in the mean number of PIM in discharge. According to Wehling et al. [24], the mean number of PIMs at discharge for the intervention group was 0.15, while the mean number of PIMs at discharge for the control group was 0.28 [24]. For an alpha risk of 0.05 and a 90% power, standard deviation 0.39, it was estimated that 189 patients would be needed per arm (378 patients in total) to detect a 0.13 reduction in the mean number of PIM [24]. Projecting a subject dropout rate of 25%, the total number of subjects required will be 500, or 250 per arm. The number of samples per trial site will be stratified based on yearly admissions. Sample size was calculated using Power and Sample size online calculator, compare two proportions, two-sample, two-sided equality test [25].

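### The sample size inputs contradict one another: SD 0.39 is too small for PIM counts with means 0.28 and 0.15, and the named two-proportions test does not give 189 per arm

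*Protocol article*

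**What the plan says.** All the inputs stand in the Sample size calculation section of the protocol article.

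- Endpoint: "Sample size was calculated based on the primary outcome: the reduction in the mean number of PIM in discharge".
- Means, taken from a cited study: "the mean number of PIMs at discharge for the intervention group was 0.15", and "the mean number of PIMs at discharge for the control group was 0.28".
- Settings: "For an alpha risk of 0.05 and a 90% power, standard deviation 0.39".
- Result: "it was estimated that 189 patients would be needed per arm (378 patients in total"), in order "to detect a 0.13 reduction in the mean number of PIM".
- Enrolment: "Projecting a subject dropout rate of 25%, the total number of subjects required will be 500, or 250 per arm".
- Calculator option: "compare two proportions, two-sample, two-sided equality test".

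The section gives no distribution for the number of PIMs per patient. It also does not name the arm to which the SD belongs.

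**The concern.** Two things do not fit together.

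First, the number of PIMs in a patient is 0, 1, 2 and so on. When the mean of such a count lies between 0 and 1, the mean alone sets a floor under the SD, whatever the distribution. The stated SD appears to lie below that floor for the control arm and for the two arms pooled.

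Second, a test of two proportions takes no SD as input, yet the section supplies an SD and also says that the two-proportions option was used. Both cannot describe the calculation that produced 189.

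This is the only power justification in the article, and it concerns one of the two primary outcomes. If the SD is too small, the 90% is overstated even before any allowance for randomising hospitals. If the test is misnamed, a reader who follows the stated method cannot reproduce the number.

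**Working it through.** **Inputs** (Sample size calculation section): control mean 0.28; intervention mean 0.15; difference 0.13; SD 0.39; two-sided alpha 0.05; power 90%; 189 evaluable and 250 enrolled per arm. The normal quantiles are 1.960 and 1.2816, with sum 3.2415 and squared sum 10.507. All figures treat patients as independent.

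**Step 1. Reproduce the stated number.** For two means, n per arm = 2 × SD² × 10.507 / difference² = 2 × 0.1521 × 10.507 / 0.0169 = 189.1. This is the stated 189 (190 if rounded up, or with a t-based formula). The arithmetic is right for a two-means comparison with SD 0.39.

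**Step 2. Try the named test.** For two proportions, 0.28 against 0.15, two-sided:

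- unpooled variance: (0.28 × 0.72 + 0.15 × 0.85) × 10.507 / 0.0169 = 0.3291 × 10.507 / 0.0169 = 204.6, so 205 per arm;
- pooled variance under the null: 208 per arm;
- with continuity correction: 223 per arm.

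None of these is 189. A one-sided test with continuity correction gives 185, but the protocol states a two-sided test.

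**Step 3. Smallest possible SD.** For a whole-number count X, X² ≥ X. Hence variance = E(X²) − mean² ≥ mean − mean² = mean × (1 − mean). Equality holds only if no patient has two or more PIMs.

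- Control: √(0.28 × 0.72) = √0.2016 = 0.449
- Intervention: √(0.15 × 0.85) = √0.1275 = 0.357
- Pooled: √((0.2016 + 0.1275) / 2) = √0.16455 = 0.406

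So 0.39 is possible for the intervention arm alone. It is not possible for the control arm, or as the common SD that the formula in Step 1 needs.

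**Step 4. Power and size with compatible SDs.** Power = Φ(0.13 / (SD × √(2/n)) − 1.960). The detectable difference at 90% power is 3.2415 × SD × √(2/n). For the Poisson row the variance equals the mean in each arm, so the pooled SD is √((0.28 + 0.15) / 2) = √0.215 = 0.464.

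| SD | Basis | n per arm for 90% | Power, 189 per arm | Power, 250 per arm | Detectable difference, 189 / 250 |
|---|---|---|---|---|---|
| 0.39 | as stated; not attainable | 189.1 | 90.0% | 96.1% | 0.130 / 0.113 |
| 0.406 | minimum possible | 205 | 87.6% | 94.8% | 0.135 / 0.118 |
| 0.464 | Poisson (assumption) | 268 | 77.8% | 88.0% | 0.155 / 0.134 |

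Example for the second row at 189: 0.13 / (0.4056 × √(2/189)) = 3.115, and Φ(3.115 − 1.960) = 0.876.

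Wider assumed SDs of 0.50 and 0.60 would give about 71% and 56% at 189 per arm. The documents supply no distribution from which to choose among these values.

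**The case against.** **The trial enrols 250 per arm, not 189.** The sizing endpoint is measured at discharge, the first assessment after admission, while follow-up runs to 18 months. Loss before discharge may be well under 25%. At the minimum SD, 205 evaluable patients per arm suffice, and 250 supply them unless more than 18% are lost (1 − 205/250 = 0.18). This stands. A reader might infer that the trial must fall short of 90% power even without clustering, and the documents do not support that. What fails is the stated claim of 90% at 189 evaluable per arm.

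**The large losses are assumed.** This also stands. Only the drop from 90% to 87.6% follows from the stated means. The figures from 78% down to 56% need patients with several PIMs. That is plausible, since eligibility requires more than five regular drugs, but the article does not quantify it.

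**The SD might be that of a change score or a residual after baseline adjustment.** The integer bound would not apply to such an SD, and the Data analysis section does speak of change over time. But the sample size section gives means at discharge in each arm and one SD beside them, and it mentions no change score, correlation or adjustment. The reading is not supported as written. If it was intended, the section should say so.

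**The test name is only a label.** Correct as far as it goes. The wrong name makes the calculation irreproducible by its stated method, but it does not itself lower the power.

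**Conclusion.** The point holds as an inconsistency among stated inputs. A common SD of 0.39 cannot occur with per-patient PIM counts averaging 0.28 and 0.15: the control SD is at least 0.449 and the pooled SD at least 0.406. The named two-sided two-proportions test gives 205 to 208 per arm, not 189.

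At 189 evaluable per arm, power is at most about 87.6%. The certain loss is therefore about 2.4 percentage points, or 16 evaluable patients per arm (205 − 189). Under an assumed Poisson variance power is about 78%. With all 250 per arm evaluable at discharge it is about 94.8% (minimum SD) or 88% (Poisson).

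These figures rest on 0.39 being the SD of the count at discharge and on independent patients. Randomising hospitals would lower power further; that is a separate matter and is not counted here.

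A reader might also object that 378 / 0.75 is 504 rather than 500. That is rounding of less than 1% and is no fault in the plan.

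**What to change.** Rewrite the Sample size calculation section as follows.

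1. Describe the calculation as a comparison of two mean counts, and delete the two-proportions description.
2. Replace 0.39 with an SD compatible with means of 0.28 and 0.15, that is at least 0.41. Show larger values, such as 0.46, as sensitivity cases labelled as assumptions. State what the SD refers to.
3. Restate the power and the detectable difference for both the planned evaluable number and the enrolled 250 per arm, together with the allowance for clustering by hospital.

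The cost is rewording and a short recalculation. The stated power at 189 per arm becomes less favourable. No additional patients need be enrolled.

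### The 90% power claim comes from a formula for individually randomised patients, but the trial randomises 14 hospitals

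*Protocol article*

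**What the plan says.** In the protocol article, the Randomization section describes a stratified cluster design "with the 14 hospitals serving as the unit of randomization". Trial setting gives the split: "seven hospitals will be randomized to intervention with the remaining seven hospitals serving as the control group".

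The Sample size calculation section sizes the trial on one endpoint: "Sample size was calculated based on the primary outcome: the reduction in the mean number of PIM in discharge". The planning values are "the mean number of PIMs at discharge for the intervention group was 0.15" and "the mean number of PIMs at discharge for the control group was 0.28", with SD 0.39, alpha 0.05 and 90% power. From these, "it was estimated that 189 patients would be needed per arm (378 patients in total) to detect a 0.13 reduction". A 25% dropout allowance then raises the total to 500, or 250 per arm.

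The section's only reference to hospitals concerns how the total is shared out: "The number of samples per trial site will be stratified based on yearly admissions". It gives no ICC, design effect or cluster size, and makes no allowance for the small number of clusters.

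**The concern.** When hospitals are randomised, patients in the same hospital share prescribers, pharmacists and local practice, so their counts of potentially inappropriate medications (PIMs) tend to be alike. The variance of the arm difference then depends on the ICC and on the number of hospitals as well as the number of patients. A calculation that treats patients as independent overstates the information in the trial.

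The 90% is a stated property of the comparison on which the trial is sized. If true power is well below that, a non-significant result would be read as evidence of no effect from a well-powered trial when the trial may have had little better than an even chance of detecting 0.13. The detectable difference is also larger than the one stated.

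**Working it through.** **Inputs from the protocol article.** Difference 0.28 − 0.15 = 0.13; SD 0.39; two-sided alpha 0.05; power 90%; 189 evaluable per arm; 25% dropout; 250 enrolled per arm; k = 7 hospitals per arm.

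**Assumption.** The document gives no ICC. It is varied here from 0.01 to 0.10. Equal hospital sizes are assumed, which favours the plan.

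**Step 1: reproduce the stated figure.** For independent patients,

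n per arm = 2 × (1.960 + 1.2816)² × (0.39/0.13)² = 189.1.

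This is the stated 189. Power at 189 per arm by the same formula is 0.8998. The design effect in the figure is therefore 1.

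**Step 2: look for a hidden allowance.** 378 / (1 − 0.25) = 504, against 500 stated. Dropout accounts for the whole increase.

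**Step 3: put the clusters back.** Evaluable patients per hospital: m = 378/14 = 27. Design effect DE = 1 + (m − 1) × ICC = 1 + 26 × ICC. Standard error of the difference = 0.39 × √(2 × DE/189). Normal-approximation power = Φ(0.13/SE − 1.960). The last column uses a noncentral t with 2 × 7 − 2 = 12 df, as for a comparison of hospital means.

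| ICC | DE | Effective n per arm | Power, normal | Power, t on 12 df |
|---|---|---|---|---|
| 0 | 1.00 | 189 | 0.900 | 0.844 |
| 0.01 | 1.26 | 150 | 0.823 | 0.755 |
| 0.02 | 1.52 | 124 | 0.748 | 0.675 |
| 0.05 | 2.30 | 82 | 0.570 | 0.502 |
| 0.10 | 3.60 | 52.5 | 0.400 | 0.349 |

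Worked line for ICC 0.05: SE = 0.39 × √(2 × 2.30/189) = 0.0608; 0.13/0.0608 = 2.137; Φ(2.137 − 1.960) = 0.570.

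**Step 4: is there a patient number that restores 90%?** With seven hospitals per arm fixed, the required number per arm is 7 × 189.1 × (1 − ICC) / (7 − 189.1 × ICC). This gives about 257 evaluable at ICC 0.01, 403 at 0.02 and 969 at 0.03. The denominator reaches zero at ICC = 7/189.1 = 0.037. From there on, an unadjusted comparison cannot reach 90% with any number of patients.

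**Step 5: detectable difference at ICC 0.05.** Normal approximation: (1.960 + 1.2816) × 0.0608 = 0.197. With the t reference on 12 df: 0.215. The plan states 0.13.

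**Step 6: the most favourable sample.** If all 250 enrolled per arm were analysed at discharge, m = 250/7 = 35.7 and power is:

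| ICC | Power, normal | Power, t on 12 df |
|---|---|---|
| 0.01 | 0.895 | 0.838 |
| 0.02 | 0.817 | 0.748 |
| 0.05 | 0.615 | 0.544 |
| 0.10 | 0.422 | 0.368 |

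On the normal approximation, 90% then survives up to ICC = (250/189.1 − 1)/(35.7 − 1) = 0.009.

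**The case against.** The best argument for the plan is that the trial is sized on PIM at discharge, the first time-point after admission, when few patients may have been lost. Much of the dropout margin could then still be available. Step 6 gives it full credit: 90% holds only up to an ICC of about 0.009 by the normal approximation, and at ICC 0.01 power on 12 df is already 84%. The plan sets that margin aside for dropout, not for clustering.

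The ICC range is assumed, and the document does not support any particular value. That limits how exactly the loss can be stated. It does not rescue the claim, because at 189 per arm any positive ICC takes power below 90%.

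Stratification by yearly admissions and adjustment for the PIM count at admission, which is to be measured, could reduce between-hospital variance. This is fair, and it makes the 0.037 ceiling conditional on an unadjusted comparison. The sample size section claims no such gain, however. Unequal hospital samples, which the plan intends, push the other way.

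The Randomization section's remarks on contamination concern the intervention spreading between people, which is not the same as correlated outcomes. The argument does not need them, since randomising hospitals is enough.

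The power figures above assume an analysis that respects clustering, whereas Data analysis names repeated measures ANOVA and t-tests and mentions no hospital term. A patient-level test that ignored clustering would reject more often, but at 189 per arm its two-sided type I error would be about 8%, 11%, 20% and 30% at ICC 0.01, 0.02, 0.05 and 0.10 (2 × Φ(−1.960/√DE)). On that reading the danger is a false positive. This does not support the 90% claim, but the restated power must name the analysis it belongs to.

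Finally, an article may leave detail to a fuller plan. This one gives a complete calculation whose result is reproduced with no clustering term, so the figure is wrong for the design and is not merely abbreviated.

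**Conclusion.** The concern holds. The arithmetic is right for individually randomised patients and wrong for this design. At the planned 189 evaluable per arm, power for 0.13 is below 90% for every ICC above zero, and it is 84% even at ICC zero if hospital means are compared on 12 df. Over an assumed ICC of 0.01 to 0.05, power runs from 82% down to 57% by the normal approximation, or from about 75% down to 50% on 12 df. These figures rest on the assumed ICC, equal hospital sizes, SD 0.39 and no covariate adjustment. Analysing all 250 per arm would soften the loss but would not restore 90% beyond an ICC of about 0.009. The claim needs correcting before the trial's result is interpreted against it.

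**What to change.** Keep the 14 hospitals and 500 patients, and rewrite the Sample size calculation paragraph as follows:

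- Withdraw the unqualified 90% and say that 189 per arm is the figure for independent patients.
- Give power for 0.13, and the difference detectable with 90% power, under the cluster design. Use DE = 1 + (m − 1) × ICC with a term for varying hospital size, and a t reference on 12 df or fewer, over a stated ICC range such as 0.01, 0.02 and 0.05. Show both 189 and 250 analysed per arm.
- Name the cluster-respecting analysis to which the restated power applies, so that it agrees with Data analysis.
- If adjustment for the PIM count at admission is planned, state the expected gain and label the assumed correlation as an assumption.
- Commit to reporting the observed ICC.

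The cost is one rewritten paragraph, a matching line in Data analysis and a less favourable power statement. No extra patients or hospitals are needed.
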